# Salivary Dysfunctions and Consequences After Radioiodine Treatment for Thyroid Cancer: Protocol for a Self-Controlled Study (START Study)

**DOI:** 10.2196/35565

**Published:** 2022-07-22

**Keywords:** radioiodine, thyroid cancer, epidemiology, self-controlled study, salivary gland, lacrimal gland, dysfunction, protocol, epidemiology

## Abstract

**Background:**

Following radioiodine (^131^I) therapy of differentiated thyroid cancer, the salivary glands may become inflamed, leading to dysfunctions and decreases in patients’ nutritional status and quality of life. The incidence of these dysfunctions after ^131^I-therapy is poorly known, and no clinical or genetic factors have been identified to date to define at-risk patients, which would allow the delivered activity to be adapted to the expected risk of salivary dysfunctions.

**Objective:**

The aims of this study are to estimate the incidence of salivary dysfunctions, and consequences on the quality of life and nutritional status for patients after ^131^I-therapy; to characterize at-risk patients of developing posttreatment dysfunctions using clinical, biomolecular, and biochemical factors; and to validate a dosimetric method to calculate the dose received at the salivary gland level for analyzing the dose-response relationship between absorbed doses to salivary glands and salivary dysfunctions.

**Methods:**

This prospective study aims to include patients for whom ^131^I-therapy is indicated as part of the treatment for differentiated thyroid cancer in a Paris hospital (40 and 80 patients in the 1.1 GBq and 3.7 GBq groups, respectively). The follow-up is based on three scheduled visits: at inclusion (T0, immediately before ^131^I-therapy), and at 6 months (T6) and 18 months (T18) posttreatment. For each visit, questionnaires on salivary dysfunctions (validated French tool), quality of life (Hospital Anxiety and Depression scale, Medical Outcomes Study 36-Item Short Form Survey), and nutritional status (visual analog scale) are administered by a trained clinical research associate. At T0 and T6, saliva samples and individual measurements of the salivary flow, without and with salivary glands stimulation, are performed. External thermoluminescent dosimeters are positioned on the skin opposite the salivary glands and at the sternal fork immediately before ^131^I administration and removed after 5 days. From the doses recorded by the dosimeters, an estimation of the dose received at the salivary glands will be carried out using physical and computational phantoms. Genetic and epigenetic analyses will be performed to search for potential biomarkers of the predisposition to develop salivary dysfunctions after ^131^I-therapy.

**Results:**

A total of 139 patients (99 women, 71.2%; mean age 47.4, SD 14.3 years) were enrolled in the study between September 2020 and April 2021 (45 and 94 patients in the 1.1 GBq and 3.7G Bq groups, respectively). T6 follow-up is complete and T18 follow-up is currently underway. Statistical analyses will assess the links between salivary dysfunctions and absorbed doses to the salivary glands, accounting for associated factors. Moreover, impacts on the patients’ quality of life will be analyzed.

**Conclusions:**

To our knowledge, this study is the first to investigate the risk of salivary dysfunctions (using both objective and subjective indicators) in relation to organ (salivary glands) doses, based on individual dosimeter records and dose reconstructions. The results will allow the identification of patients at risk of salivary dysfunctions and will permit clinicians to propose a more adapted follow-up and/or countermeasures to adverse effects.

**Trial Registration:**

ClinicalTrials.gov NCT04876287; https://clinicaltrials.gov/ct2/show/NCT04876287

**International Registered Report Identifier (IRRID):**

DERR1-10.2196/35565

## Introduction

Approximately 10,600 new cases of thyroid cancer were diagnosed in France in 2018, and this incidence has increased by an average of 4.4% per year between 1990 and 2018 [1]. Although incidence rates are steadily increasing, mortality rates have declined slightly in recent decades, and thyroid cancer has an excellent prognosis with a 10-year survival rate of over 90% [1].

Standard treatment for differentiated thyroid cancer is thyroidectomy followed by radioiodine (^131^I) ablation [2]. This ^131^I complementary therapy aims to destroy thyroid remnant tissues, thus facilitating biological surveillance via the thyroglobulin dosage and reducing the risk of cancer relapse. This therapy also treats possible persistent or metastatic diseases, and enables assessment of disease extension through posttherapy scintigraphy. However, the usefulness of ^131^I-therapy is debated, especially for cancers with a low risk of recurrence because of their excellent survival rate, and the possibility of adverse effects of this therapy in the short, medium, and long term [3]. The salivary gland might be a site of inflammation after ^131^I-therapy owing to its ability to capture and concentrate iodine [4], and in particular radioactive iodine, which may be symptomatic in the acute phase, and can be followed by chronic salivary dysfunctions [5]. Such dysfunctions are defined as any quantitative or qualitative change in saliva production, such as a decrease in salivary secretion ranging from minor to severe hypofunction [6]. Nevertheless, saliva is crucial for the maintenance of buccal health. Notably, the incidence of salivary dysfunctions is still unclear, ranging from 2% to 67%, due to major methodological differences between studies, including the method and timing of identification of salivary dysfunctions [4].

Salivary dysfunctions may lead to an increased risk of inflammation and/or oral infection, a change in the taste of food, and difficulties in swallowing and digestion. Lacrimal gland dysfunctions (one of the diagnostic criteria for Sjögren syndrome) have also been reported after ^131^I-therapy, suggesting that some patients may develop simultaneous lacrimal and salivary gland dysfunctions in the years following ^131^I-therapy [7]. Quality of life after ^131^I-therapy requires special attention because of the good prognosis of differentiated thyroid cancer. In the context of ^131^I-therapy for thyroid cancer, few studies have assessed the long-term quality of life at 6 months or later after ^131^I-therapy [8-12], whereas it has been shown that salivary dysfunction assessed by a specific questionnaire may occur more than 6 months after therapy for 25% of patients [13]. Moreover, there are inconsistencies in the reported relationships between objective measures of salivary flow (sialometry) and subjective measures of salivary dysfunction (self-questionnaire) [6,11], reinforcing the need to assess salivary dysfunction by creating a composite criterion combining objective and subjective measures.

Additionally, the dose-response relationships between ^131^I-therapy and the incidence of salivary and lachrymal dysfunctions have been rarely studied, and the administered activity is typically used as a proxy for the dose absorbed by the salivary glands. However, the administered activity does not accurately reflect the dose received by the salivary glands due to the variation in iodine uptake ability of the salivary gland, which could be modified by the size of the thyroid remnant tissues or a potential iodine deficiency of the patient before treatment, along with the inherent interpatient variability affecting the entire biokinetics of iodine. The use of an adapted dosimetric method using thermoluminescent dosimeters and anthropomorphic phantoms would make it possible to better estimate the dose-response relationship by estimating the absorbed dose to the salivary gland.

Finally, while a strong interrelationship between epigenetic processes and genetic factors associated with dry mouth syndrome has been shown [14], the potential existence of individual genetic sensitivity to ^131^I in mediating the relationship between ^131^I exposure and salivary dysfunctions is important to study, especially as specific epigenetic changes could lead to increased sensitivity to ionizing radiation [15]. Other risk factors of salivary dysfunctions in the context of thyroid cancer treated by ^131^I-therapy are poorly understood. Only one study investigated the relationship between salivary flow and age, gender, or pathological tumor-node-metastasis (TNM) staging, but did not show any significant relationship, potentially owing to a lack of statistical power due to the small number of patients included (N=67) [11], emphasizing the importance of setting up a study with a large number of patients. Increased knowledge of these factors would help to identify the patients at risk of developing salivary dysfunctions, which could possibly help to adapt the treatment and follow-up accordingly.

In this context, the Salivary dysfuncTions After Radioiodine Treatment (START) study was launched in September 2020, with the following objectives: (1) to estimate the mid- and long-term incidence of salivary dysfunctions in patients with thyroid cancer treated with ^131^I, using objective, subjective, and mixed criteria; (2) to highlight risk factors of posttreatment salivary dysfunctions using clinical, pathological, biomolecular, and biochemical factors; (3) to validate a dosimetric method to calculate the dose absorbed by the salivary gland; (4) to estimate the dose-response relationship between exposure of the salivary glands to ^131^I and salivary dysfunctions; and (5) to investigate the consequences of salivary dysfunctions on the quality of life and nutritional status of patients.

## Methods

### Study Design

START is a prospective self-controlled study that includes patients with thyroid cancer who underwent thyroidectomy and are candidates for complementary ^131^I-therapy. This research program aims to enroll 120 patients from the nuclear medicine department of Pitié-Salpêtrière Hospital (Paris, France), divided into two groups of 40 and 80 patients treated with ^131^I activity of 1.1 GBq and 3.7 GBq, respectively, thus expecting a high number of patients with salivary dysfunctions to provide good statistical power for the analyses.

All consecutive patients awaiting ^131^I-therapy are systematically invited to participate in the study. They are enrolled just prior to the ^131^I capsule administration (ie, 1 to 3 months after thyroidectomy), and have three follow-up points: at enrollment (T0), and at 6 months (T6) and 18 months (T18) after ^131^I-therapy (Figure 1).

**Figure 1 figure1:**
[figure not shown]
Timeline summarizing the study's outline. T0: enrollment; T6: 6 months after radioiodine (^131^I) therapy; T18: 18 months after radioiodine therapy.

### Inclusion and Exclusion Criteria

To be included, patients must have undergone thyroidectomy for the treatment of a differentiated thyroid cancer, be a candidate for complementary ^131^I-therapy, be over 18 years of age, be willing to participate in the study, and have signed a consent form. Patients who have previously been treated with ^131^I or who are likely to be treated with multiple ^131^I therapies within 18 months of inclusion are excluded.

### Ethical Considerations

This study will be conducted in accordance with the Declaration of Helsinki (amended at the 64th World Medical Association General Assembly, Fortaleza, Brazil, October 2013) and in accordance with the principles of “Good Clinical Practice” and the Medical Research Involving Human Subjects Act (WMO) [16].

Approvals from the local ethical committee have been received (Comité de Protection de Personnes Sud Mediterranée III, ID 20.01.24.56149; and Agence Nationale de Sécurité des Médicaments, ID 2020-A00208-31). The protocol is registered and will be posted on the ClinicalTrials.gov public website under the number NCT04876287.

Patients included in the study must sign a consent form in which they certify that they have understood the objectives and procedures of the research in which they will participate. They certify that they have had time to think and ask questions to come to an informed decision to participate, and they are aware that this study is not mandatory in the context of their therapy and that they can withdraw at any time.

### Conduct of the Study

#### Schedule

The START study is expected to be carried out from September 2020 until October 2022, including three measuring points for each patient: at enrollment, and at 6 and 18 months later.

#### Before Enrollment

The investigating physician in the nuclear medicine department enables first contact with patients during the postsurgery consultation. During this first visit, the physician introduces the START study and its objectives to the patients for whom ^131^I-therapy is planned, informs them about the nature of the constraints and the expected benefits of the research, and answers all of the patient’s questions. The physician ensures that patients meet the inclusion criteria. If the inclusion criteria are fulfilled, a study information leaflet detailing the protocol is given to the patient with the consent form.

#### Enrollment Visit (T0)

The enrollment visit occurs when an eligible patient has given consent to participate in the study. This visit takes place at the hospital during the consultation prior to the complementary ^131^I-therapy (on the day of treatment, approximately 2 months after surgery) in a face-to-face manner with a clinical research associate. Clinical and personal data and saliva samples are collected, self-administered questionnaires are provided to patients (see Data Collection section below and Multimedia Appendix 1), and the patients are equipped with thermoluminescent dosimeters (see Dosimetry section below) just before administration of the ^131^I-therapy. The dosimeters will be removed by the physician 5 days later, immediately before the posttherapy scan.

#### Six-Month Follow-up (T6)

The 6-month follow-up takes place during the posttherapy consultation at the Thyroid and Endocrine Tumors Unit, Institute of Endocrinology (E3M), Pitié-Salpêtrière Hospital (Paris, France), in a face-to-face manner with a clinical research associate. During this visit, clinical and personal data collection, saliva samples, and self-questionnaires are again carried out

#### Eighteen-Month Follow-up (T18)

Patients are called by phone to answer the self-questionnaires with a clinical research associate.

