### Data Collection

All data are collected using paper versions, and are then entered and recorded on a secure server (Table 1).

All questionnaires are completed at each measuring point of the study for each patient. Questionnaires have been selected on the basis of ease and speed of administration by an interviewer, peer-validated, and on the fact that they are the most widely used questionnaires in this type of research (see Multimedia Appendix 1).

Saliva sampling has been performed according to a standardized methodology (see Multimedia Appendix 2).

**Table 1 table1:** Summary of data collection.

Data type	Qualitative data	Quantitative data
Thyroid cancer information (collected only at the enrollment visit)	Size of the postsurgery remnant, tumor histology, pTNM^a^ staging, Tg^b^ stimulation protocol, family history of thyroid cancer, patient history of cancer or comorbidities, prescribed activity of ^131^I (1.1 or 3.7 GBq)	Surgery to therapy duration (months)
Clinical data	Self-rated menopausal status, all medications used during the last 3 months, tobacco and alcohol consumption, self-palpation of the salivary glands (normal, painful, or swollen), self-reported oral carries or infections, observed cracked lips, self-reported use of a saliva substitute, sialagogue	Age, height, weight
Questionnaires	Salivary complaints questionnaire; eye dryness, OSDI^c^ questionnaire; questions about nutrition; anxiety and depressive symptoms (HAD^d^ scale)	Physical and mental composite scores about quality of life (MOS SF-36^e^)
Saliva samples	Not applicable	Weight (precision 0.01 mg), volume (precision 0.01 mL), electrolyte concentrations (mmol/L: sodium, potassium, chloride, amylase, and total protein composition), genetic and epigenetic variant proportions

^a^pTNM: pathological tumor-node-metastasis.

^b^Tg: thyroglobulin.

^c^OSDI: Ocular Surface Disease Index.

^d^HAD: Hospital Anxiety and Depression.

^e^MOS SF-36: Medical Outcome Study Short Form 36 items.

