#### Secondary Endpoints

Secondary endpoints are defined as follows: change in quality-of-life score between T0, T6, and T18; change in nutrition between T0, T6, and T18; change in chemical saliva composition between T0 and T6; change in anxiety and depression symptoms between T0, T6, and T18; genetic and/or epigenetic variant identification that may modify the risk of salivary dysfunctions after ^131^I-therapy; identification of individual factors associated with salivary dysfunctions at T6 and T18; and dose-response analysis between the ^131^I-dose received precisely at the salivary glands and salivary dysfunctions at T6 and T18.

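### Salivary flow is not measured at T18, so objective and mixed dysfunction cannot be estimated there, and the T18 dysfunction outcome needs its own questionnaire-based definition

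*Protocol article*

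**What the plan says.** **What is measured when.** The Abstract (Methods) states: "At T0 and T6, saliva samples and individual measurements of the salivary flow, without and with salivary glands stimulation, are performed". The T6 section agrees: "During this visit, clinical and personal data collection, saliva samples, and self-questionnaires are again carried out". For T18 the protocol article says only: "Patients are called by phone to answer the self-questionnaires with a clinical research associate". Data Collection adds: "All questionnaires are completed at each measuring point of the study for each patient".

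**What is to be estimated.** Objective 1, at the end of the Introduction, is the "mid- and long-term incidence of salivary dysfunctions in patients with thyroid cancer treated with ^131^I, using objective, subjective, and mixed criteria". The Secondary Endpoints include "identification of individual factors associated with salivary dysfunctions at T6 and T18" and a dose-response analysis of salivary dysfunctions at the same two visits. The closing paragraph of the Results repeats the two visits for the dose-response relationship.

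**How dysfunction is defined.** The primary endpoint is a composite at T6. It joins an objective part (unstimulated flow below 0.2 mL/min, stimulated flow below 0.7 mL/min, or both) to a subjective part (discomfort, parotid pain, swallowing difficulty or dry eyes). No separate definition is given for T18.

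**The concern.** Objective 1 and the two secondary endpoints use one term for visits at which different data exist. Two things are at stake.

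- A reader of objective 1 will expect long-term incidence by measured flow and by the mixed criterion. The design cannot supply either.
- If the T6 models use the composite and the T18 models use questionnaire answers, a difference between the T6 and T18 risk factors, or between the two dose-response curves, could come from the change of outcome and not from the course of the condition.

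The protocol article itself makes the second point serious. Its Introduction reports that flow measurements and self-reported dysfunction are inconsistently related in earlier work, and gives this as the reason for building a composite. On that argument, a questionnaire outcome at T18 cannot stand in for the T6 composite.

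**Working it through.** The documents give no figure for this point, so the check is mainly a comparison of sections.

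**Step 1. Which criterion can be computed at which visit?**

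| Criterion | Data needed | T0 | T6 | T18 |
|---|---|---|---|---|
| Objective | Measured flow | yes | yes | no |
| Subjective | Questionnaire items | yes | yes | yes |
| Mixed (composite) | Flow and questionnaire items | yes | yes | no |

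Sources: Abstract (Methods), the three visit sections, Data Collection, Primary Endpoint.

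**Step 2. Which visit can be the long-term one?** There are two visits after treatment, T6 and T18. If mid-term and long-term are separate horizons, long-term can only be T18. Objective 1 then asks for two criteria that Step 1 shows to be empty there. The two secondary endpoints name T18 outright, so for them nothing depends on the labels.

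**Step 3. Is the limit respected elsewhere?** Yes. The Secondary Endpoints restrict the change in saliva composition to T0 and T6. No such restriction, and no T18 definition, is attached to dysfunction.

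**Step 4. Could the change of outcome matter?** This illustration uses assumed prevalences that are not in the documents. Let the subjective prevalence be s = 30% and the flow-based prevalence o = 5% to 30%, both unchanged from T6 to T18. Let k = 0 mean independence and k = 0.5 mean halfway to the greatest possible overlap.

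- Both criteria met: B = o·s + k·(min(o, s) − o·s)
- Either criterion met: E = o + s − B

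| o | k | B | E |
|---|---|---|---|
| 5% | 0 | 0.05 × 0.30 = 1.5% | 5 + 30 − 1.5 = 33.5% |
| 5% | 0.5 | 1.5 + 0.5 × (5 − 1.5) = 3.25% | 5 + 30 − 3.25 = 31.75% |
| 30% | 0 | 0.30 × 0.30 = 9% | 30 + 30 − 9 = 51% |
| 30% | 0.5 | 9 + 0.5 × (30 − 9) = 19.5% | 30 + 30 − 19.5 = 40.5% |

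A subjective-only T18 outcome would be 30% throughout. With no clinical change, an either-criterion composite at T6 (31.75% to 51%) would appear to fall by 1.75 to 21 points. A both-criteria composite (1.5% to 19.5%) would appear to rise by 10.5 to 28.5 points. The Primary Endpoint section says that the two parts are combined, and the analysis summary calls the composite a sum of dysfunctions. Neither settles the rule, so the direction of the artefact is also open.

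**The case against.** The strongest reply is that the article never names the composite or the flow criterion at T18. The composite is fixed at T6. Subjective dysfunction is recognised in its own right in the Introduction and in the list of outcomes, and the questionnaires are repeated at every visit. A questionnaire-based outcome is then the natural reading at T18, and its details may sit in the full protocol. The time labels are also loose: the Introduction counts 6 months or later as long-term for quality of life, while the Discussion speaks of early and mid-term toxicity.

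Much of this stands. It rules out several stronger readings that a reader might infer:

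- *Every T6-to-T18 comparison mixes definitions.* It does not. Subjective salivary complaints, eye dryness, quality of life, nutrition, and anxiety and depression use the same instruments at both visits.
- *Dysfunction is defined only through flow.* The cut-offs define the objective part. The subjective part is listed separately.
- *Patients who qualify by flow alone become non-cases at T18, so prevalence falls by 6 to 18 points.* That range is the planned 60% multiplied by an assumed flow-only share of 10% to 30%. It also needs an either-criterion rule and unmeasured flow scored as normal. None of the three is in the documents, and the 60% is a literature rate not stated to apply to this composite.

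The reply does not rescue objective 1, which puts both horizons and all three criteria in one sentence. Nor does it make the T6 and T18 outcomes the same if the composite is used at T6.

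**Conclusion.** The point holds in limited form. With flow taken only at T0 and T6, the objective and mixed criteria have no observations at T18. Objective 1 cannot be delivered as written if its long-term horizon is T18. The factor and dose-response endpoints cannot use one outcome at both visits if the composite or flow criterion is used at T6.

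The size of any artefact cannot be derived from the documents. The ranges shown under assumed prevalences demonstrate only that it could be material and could go either way.

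The T6 primary endpoint and the sample size are untouched. This is therefore a correction of scope and definition, not a fault in the main analysis. It is best made before the T18 data are analysed, because T18 follow-up was already running at publication and a definition chosen afterwards could be influenced by the results.

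**What to change.** 1. In objective 1, limit incidence by objective and mixed criteria to T6, and describe long-term incidence as subjective only.
2. State that dysfunction at T18 is a subjective outcome, computed from the same questionnaire items at T0, T6 and T18. Use only items present at all three visits: Table 1 lists self-palpation of the glands under clinical data, which the T18 section does not mention.
3. Keep the T6 composite analysis. In addition, run the T6 factor and dose-response models on the subjective outcome, and use that outcome for any contrast of T6 with T18.
4. Name the move from face-to-face to telephone contact as a limitation of that contrast. The documents give no basis for sizing its effect.

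The cost is the wording of one objective and two secondary endpoints, plus one additional set of T6 models. No new data are needed. The claim to long-term objective incidence is given up, but the design could not support it.
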